### 3.2. Study Participants—Eligibility Criteria

The study was conducted in accordance with the Declaration of Helsinki. As shown in Figure 1, the participants were recruited from the Diet and Healthy Ageing Study (DaHA) (NUS-IRB Reference No:10-517) [41], a longitudinal cohort study based at the Training and Research Academy at Jurong Point (TaRA@JP). The research nurses, research assistants, and [name] obtained written informed consent from the potential participants before screening for potentially eligible participants. All potential participants were screened for cognitive status and other eligibility criteria based on *a priori* inclusion and exclusion criteria.

The inclusion criteria were:(1)Community-dwelling older adults aged between 60 and 85 years old and fulfilled the Peterson’s operational criteria of mild cognitive impairment [42]:
At least one age-education adjusted neurocognitive test Z-score < −1.5;Do not meet DSM-IV criteria for major neurocognitive disorder;Memory/cognitive complaint, corroborated by a reliable informant;Intact activities of daily living.
(2)Function independently.(3)Able to travel on their own to TaRA@JP and participate in the study.(4)Does not have a diagnosis of dementia.

The exclusion criteria were:(1)Dementia or normal ageing;(2)Diagnosed with a neurological condition (e.g., epilepsy, Parkinson’s disease);(3)Diagnosed with major psychiatric condition (e.g., major depressive disorder);(4)Suffer from a terminal illness (e.g., cancer);(5)Had significant visual or hearing impairment;(6)Had marked upper and lower limb motor difficulties, which may affect their ability to participate in the study;(7)Participation in another interventional study concurrently.

It is noteworthy that we did not exclude participants who did not consent to provide bio-specimen or MRI scans. In such cases, we continued with collecting all other measures to which the participants have consented, including interventions and neurocognitive outcome assessments. All participants were also newly-diagnosed community-dwelling MCI participants, who were naïve for medications targeting cognitive impairment at the start of the study.

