### 3.10. Statistical Analysis

Based on previous studies [35,49,50,51] examining the effects of mindfulness on the means and SDs for co-primary outcomes chosen for this study, i.e., fluid biomarkers and neurocognitive tests, we estimated the effect sizes to be 0.5. Hence, we required 24 participants in each group to have a power of 80% to detect statistical significance at 5% level. Considering a potential 20% drop-out rate, 30 participants needed to be assigned to each group at baseline. Hence, the targeted total sample size was 60.

All demographic and outcome measures were expressed as mean ± standard deviation (SD). We used either Fisher’s exact, Student’s or chi-square *t*-test to examine the differences in the baseline variables, as per the nature of the data. In the event the raw values of the measures were not conforming to the normality assumption, the raw values were natural log-transformed for subsequent analyses. Successful normalizations were based on dot plots, skewness, and kurtosis.

We employed the linear-mixed model to examine the treatment effects of MAP on the biomarkers and psychometric scale outcome measures, compared to the active control group, HEP, over the three time-points. For the psychometric and fluid biomarker measures, we performed intention-to-treat analyses using linear-mixed model, because it is robust to missing data. The model considers all the participants included in the baseline, regardless of whether they have missing values at subsequent follow-ups [52]. For the neuroimaging measures, since the drop-out rates were much higher, we used per-protocol analyses, where only participants that completed the intervention and had neurocognitive and neuroimaging scans at follow-ups were included in the ANOVA analyses.

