**Figure 4 ijerph-18-10205-f004:**
[figure not shown]
CONSORT 2010 Flow diagram for co-primary outcome measures.

**Table 1 ijerph-18-10205-t001:** A summary of assessments or measures collected throughout the three time-points.

Assessments or Measures	Baseline	At 3-Month	At 9-Month
Social-demographic Questionnaire	√	-	-
Basic Health Screening	√	√	√
Physical Assessments (ADL and IADL)	√	√	√
Mini Mental State Examination (MMSE)	√	√	√
Depression and Anxiety Screening Tests (GDS and GAI)	√	√	√
Clinical Dementia Rating (CDR) Scale	√	√	√
Neurocognitive Tests	√	√	√
MRI Brain Scan	√	√	-
Blood Sample	13 mL	8 mL	13 mL
Urine Sample	15 mL	-	15 mL
Fecal Sample	√	√	√
Saliva Sample	√	√	√

ADL = Activities of Daily Living; IADL = Instrumental Activities of Daily Living; MMSE = Mini-Mental State Examination; GDS = Geriatric Depression Scale; GAI = Geriatric Anxiety Inventory; CDR = clinical dementia rating; MRI = Magnetic Resonance Imaging.

**Table 2 ijerph-18-10205-t002:** Comparisons of the baseline demographic and characteristics between participants in the Mindful Awareness Practice (MAP) and Health Education Program (HEP) Arms (N = 55).

Baseline Demographics and Characteristics	MAP, Treatment; n (%) or Mean (SE) (n = 28)	HEP, Control; n (%) or Mean (SE) (n = 27)	*p*-Value
Age (in years)	71.89 (1.14)	70.67 (1.19)	0.46
Sex			
Male	8 (28.60%)	6 (22.20%)	0.59
Female	20 (71.40%)	21 (77.80%)	
MCI subtypes			
aMCI	13 (46.40%)	8 (29.6%)	0.27
Non-aMCI	15 (53.6%)	19 (70.4%)	
Years of Formal Education	5.27 (5.02)	3.44 (4.27)	0.16
Ethnicity			
Chinese	27 (96.40%)	27 (100%)	1.00
Indian	1 (3.60%)	0 (0%)	
Others	0 (0%)	0 (0%)	
Employment Status			
Retired	14 (51.90%)	11 (40.70%)	0.14
Full-time worker	0 (0%)	0 (0%)	
Part-time worker	0 (0%)	4 (14.80%)	
Housewife	13 (48.10%)	12 (44.40%)	
Marital Status			
Single	1 (3.70%)	0 (0%)	0.29
Married	18 (66.70%)	14 (51.90%)	
Divorced	2 (7.40%)	1 (3.70%)	
Widowed	6 (22.20%)	12 (44.40%)	
MMSE (Total Scores)	24.59 (0.63)	24.70 (0.75)	0.91
GDS			
<5	18 (64.30%)	22 (81.50%)	0.15
≥5	10 (35.70%)	5 (18.50%)	
Attendance rate (%)	88.6 (12.48)	87.0 (19.11)	0.77
Total number of metabolic disorders	1.44 (0.22)	1.52 (0.16)	0.79
Presence of diabetes	6 (22.2%)	8 (29.6%)	0.76
BMI, kg/m^2^	24.76 (0.85)	24.06 (0.67)	0.53
Total number of chronic diseases	2.04 (0.33)	2.85 (0.25)	0.66
Total number of medications taken	2.89 (0.44)	2.96 (0.39)	0.90
Total number of participants taking psychotropic medications	1 (3.70%)	0 (0%)	1.00

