Abbreviations: aMCI = amnestic MCI; non-aMCI = non-amnestic MCI; BMI, body mass index; MMSE, Mini-Mental State Examination; GDS, Geriatric Depression Scale; clinical cut-off for GDS is 5, with those ≥5 suggesting probable depression.

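### The normality rule checks raw values rather than model residuals and offers only a natural log, which does not suit scores that can be zero or are left-skewed

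*Protocol article*

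**What the plan says.** Section 3.10 (Statistical Analysis) sets one rule for all measures. The trigger is "In the event the raw values of the measures were not conforming to the normality assumption", and the remedy is that "the raw values were natural log-transformed for subsequent analyses". The following sentence adds a check: "Successful normalizations were based on dot plots, skewness, and kurtosis". No step is given for a measure that fails it.

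The mixed model is then used "to examine the treatment effects of MAP on the biomarkers and psychometric scale outcome measures", so bounded scores fall under the rule together with fluid biomarkers. Table 1 lists "Depression and Anxiety Screening Tests (GDS and GAI") at all three time-points, as well as MMSE, CDR, ADL/IADL and the neurocognitive tests.

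Section 3.10 also puts the baseline value of the outcome into every model as a covariate, and says that anyone measured at one or more time-points is included.

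**The concern.** There are three separate problems.

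- **Trigger.** The normality assumption of a linear mixed model concerns residuals and random effects, given arm, time, baseline, age, sex and education. A skewed raw distribution does not show that the assumption fails, and a symmetric one does not show that it holds.
- **Zeros.** The log of zero does not exist, and statistical software returns it as missing. On a symptom scale the zeros are the participants without symptoms, so any loss would be selective. If the baseline covariate is logged too, a participant with a baseline zero has a missing covariate and leaves the model at every visit. That would contradict the stated inclusion rule. The mixed model's tolerance of missing outcomes does not extend to missing covariates.
- **Left skew.** The log is concave, so it stretches the lower tail. A score crowded near its maximum becomes more skewed.

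At stake are who is analysed, and how well the model fits, for any bounded score to which the rule was applied. For strictly positive, right-skewed biomarkers the log is a sound choice.

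**Working it through.** The plan gives no figure that depends on this rule, so there is nothing to reproduce. The checks below show direction and plausible range only.

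**Inputs from the article (Table 2 and its footnote)**

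- GDS below 5: 18/28 in MAP and 22/27 in HEP, pooled 40/55 = 72.7%. So 15/55 = 27.3% are at or above 5. The footnote confirms "clinical cut-off for GDS is 5".
- MMSE, mean (SE): 24.59 (0.63) with n = 28, and 24.70 (0.75) with n = 27.

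**Assumptions, not in the article:** GDS is a count starting at zero, with a maximum of 15 where a maximum is needed; MMSE runs from 0 to 30; the distribution shapes named below.

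**Check 1: how many GDS scores could be zero?** Each model is matched to P(GDS ≥ 5) = 15/55.

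| Assumed distribution | Share at zero | Of 55 |
|---|---|---|
| Beta-binomial 0-15, near-binomial | 1.8% | about 1 |
| Poisson, mean 3.49: exp(-3.49) | 3.0% | about 2 |
| Beta-binomial, dispersion parameter 10 | 11% | about 6 |
| Geometric: 1 - (15/55)^(1/5) | 23% | about 13 |
| Beta-binomial, dispersion parameter 3 | 28% | about 16 |
| Beta-binomial, dispersion parameter 1.5 | 41% | about 23 |

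The range of about 1 to 23 of 55 mostly reflects the choice of model. It is not an estimate for this trial.

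**Check 2: what would the log do to MMSE?** SD = SE × √n:

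- MAP: 0.63 × √28 = 3.33
- HEP: 0.75 × √27 = 3.90

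Skewness before and after the log, for distributions on 0-30 matched to these means and SDs:

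| Arm | Shape | Raw | After log |
|---|---|---|---|
| MAP | Beta | -0.89 | -1.43 |
| HEP | Beta | -1.03 | -1.73 |
| MAP | Beta-binomial | -0.74 | -1.28 |
| HEP | Beta-binomial | -0.92 | -1.64 |
| MAP | Beta-binomial, 15 and above only | -0.58 | -0.93 |
| HEP | Beta-binomial, 15 and above only | -0.65 | -0.99 |

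The size depends on the shape, but the skew worsens in every row.

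**Check 3: would a small patch be enough?**

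- ln(x + 1) keeps every GDS zero. Modelled skewness goes from +1.28 to +0.28 (dispersion parameter 2), but from +0.79 to -0.47 (parameter 10).
- Reflected MMSE, ln(31 - x), in the full-range beta-binomial gives -0.72 (MAP) and -0.56 (HEP).

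An added constant solves the zeros. Neither device reliably solves the skew, and neither corrects the trigger.

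**The case against.** The strongest reply is that the harm is inferred. A reader might take the rule to mean that symptom-free participants were dropped from an analysis described as intention-to-treat. That would need GDS or GAI to be judged non-normal, to contain zeros, and to be logged without an added constant. The article reports none of these. A constant is a detail that an article may leave to the full plan, and the stated intent is to include everyone with a measurement. This reply stands, so the loss of participants can be put only conditionally.

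Second, the article checks normalization after the transformation, and that check could well expose a worsened MMSE skew. This also stands. One cannot say that badly fitting models were kept, only that the article names no route once the check fails.

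Third, some supporting arguments go further than the text:

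- Negative Z-scores appear only in an eligibility criterion; the article does not say that outcomes are analysed as Z-scores.
- "Intact activities of daily living" at entry suggests clustering, but no scoring range or direction is given for ADL/IADL.
- GDS and GAI are secondary outcomes, and MMSE is listed apart from the neurocognitive tests. No co-primary test is shown to be zero-valued or left-skewed.

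What the reply does not remove is the raw-value trigger and the single remedy for all measures. Both are written in the article, and an added constant would change neither.

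**Conclusion.** The concern holds in a limited form. The rule tests raw values where the model's assumption concerns residuals, and it names one transformation that cannot be computed at zero and that worsens left skew. Read literally, a logged baseline of zero would remove a participant whom Section 3.10 says is included.

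The size is unknown. The figures for zeros rest on an assumed GDS range and shape. The MMSE figures rest on an assumed 0-30 range and shape. Whether either scale met the rule's trigger is not stated. The documents do not support a claim that participants were excluded or that any published result is wrong.

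This is a cheap improvement of minor severity, confined to bounded scores. It does not count against logging positive, right-skewed biomarkers.

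**What to change.** The article's Trial Status section says that data collection is complete, some analyses are published and others are pending.

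For the remaining analyses:

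1. Judge normality on the residuals of the fitted model, not on raw values.
2. Use the natural log only for strictly positive, right-skewed measures, mainly fluid biomarkers, and report geometric mean ratios.
3. Keep bounded cognitive, affective and functional scores on their original scale, with bootstrap or robust standard errors if residuals are poor.

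For outcomes already published, state which measures were logged and how zeros were handled, and report a raw-scale sensitivity analysis for any score that was logged.

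The cost is small: syntax changes for the pending analyses, some re-running for published scores that were logged, and slightly less uniform reporting, with ratios for some outcomes and differences for others. Count or ordinal mixed models are optional. Psychometric losses of 10 and 8 leave 55 - 18 = 37 participants at 9 months, so they involve a trade-off and are not required.

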## Abstract

Background: With an aging population, developing non-pharmacological interventions (NPIs) to delay dementia has become critical. Apart from cognitive decline, dementia is associated with multiple pathophysiology, including increased oxidative stress, dysregulated gene expressions, cytokine, neurotrophin, and stress markers, telomere shortening, and deteriorations in brain connectivity. Although mindfulness practices have been proposed to ameliorate these biological changes, no empirical studies were conducted. We thus aimed to investigate the effects of mindfulness awareness practice (MAP) to prevent cognitive decline and improve peripheral biomarkers in community-dwelling older adults diagnosed with mild cognitive impairment (MCI). Methods/Design: This was a single-blinded and parallel-group randomized controlled trial with two arms (intervention and active control arms), conducted over nine months. A total of 60 consenting community-dwelling older adults diagnosed with MCI were planned to be randomized in a 1:1 ratio to either the MAP or the Health Education Program (HEP). Interventions were performed weekly for the initial 12 weeks, and monthly for the subsequent six months. Outcome measures were assessed at baseline, 3-month, and 9-month post-intervention by blinded assessors. Primary outcomes were neurocognitive tests, comprehensive peripheral biomarkers, and brain imaging scans. Secondary outcomes included basic health screening measures, affective symptoms, and measures of physical functions. Linear-mixed models were used to examine the effects of MAP on these outcome measures. Significance: This is the first randomized controlled trial to systematically investigate the effects of a mindfulness intervention in improving cognitive functions and various biomarkers in community-dwelling older adults diagnosed with MCI. Our findings have the potential to inform mindfulness intervention as a novel approach to delay dementia.

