In each of the linear-mixed models, we entered the outcome measure of interest as the dependent variable. The time-points of the intervention, treatment arm, and an interaction term between time-points and treatment arm were treated as the independent variables. Covariates for all the models included the baseline values of the respective outcome variable, age, sex, and years of formal education. We also collected measures for other covariates relevant to MCI and dementia, including the geriatric depression scale (GDS) and geriatric anxiety inventory (GAI) clinical cut-offs, history of cardiovascular diseases, and history of myocardial infarction. These additional covariates were explored to examine their effects on the basic models, using the model fit statistics, namely the Akaike information criterion (AIC) and Bayesian information criterion (BIC) values. In the final models, for the additional covariates, only the significant ones for each model were retained. We based all the analyses on the intention-to-treat principle, hence all the participants who had measures at at least one time-point were included in the analysis. All statistical analyses were and will be further performed using the Statistical Package for the Social Sciences (SPSS) Statistics for Windows, version 23.0 (IBM Corp., Armonk, NY, USA). A two-tailed *p*-value of < 0.05 was and will be considered statistically significant.

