### 4.3. Maintenance: Adherence Rate and Lost to Follow-Up for Primary and Secondary Outcome Measures

Adherence or attendance rates were approximately 88 and 89% for the MAP and HEP groups, respectively. Since we did not require all the participants to consent to bio-specimen collection and neuroimaging scans, there could be differences in lost to follow-ups. Lost to follow-ups for fluid biomarker, psychometric and neuroimaging measures are presented in Figure 4.

For the fluid biomarker measures, the total number of lost to follow-up cases at 9-month time-point was 9 in the MAP (32.14%) and 6 (22.22%) in the HEP group. For the psychometric measures, similar lost to follow-up rates at 9-month time-point were observed: 10 in the MAP (35.71%) and 8 in the HEP group (29.63%). For the neuroimaging measures, there were 18 lost to follow up cases in the MAP (64.29%) and 21 lost to follow up cases in the HEP group (77.78%).

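### Neuroimaging, listed as a primary outcome, is analysed by ANOVA in intervention completers only, which conflicts with the article's intention-to-treat statement and with the Abstract's mixed-model statement

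*Protocol article*

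**What the plan says.** **Status and method in the Abstract.** "Primary outcomes were neurocognitive tests, comprehensive peripheral biomarkers, and brain imaging scans". The Abstract continues: "Linear-mixed models were used to examine the effects of MAP on these outcome measures". On timing it says: "Outcome measures were assessed at baseline, 3-month, and 9-month post-intervention by blinded assessors".

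**Section 3.10, psychometric and fluid biomarker measures.** "we performed intention-to-treat analyses using linear-mixed model, because it is robust to missing data".

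**Section 3.10, neuroimaging.** Giving much higher drop-out as the reason, the text says "we used per-protocol analyses, where only participants that completed the intervention and had neurocognitive and neuroimaging scans at follow-ups were included" in an ANOVA.

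**Section 3.10, general rule.** "We based all the analyses on the intention-to-treat principle". The sentence goes on to include everyone with data from one time-point or more.

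**Section 3.10, sample size.** Only fluid biomarkers and neurocognitive tests are named as co-primary. Imaging is not mentioned.

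**Section 4.3.** Imaging losses are 18 in MAP (64.29%) and 21 in HEP (77.78%). They carry no time-point, whereas the fluid and psychometric losses are given at 9 months.

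**Table 1.** The row "MRI Brain Scan" is ticked at baseline and 3 months and has a dash at 9 months.

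**The concern.** A primary outcome has two incompatible analysis descriptions. A reader of the Abstract or of the general rule would expect a mixed model in everyone with a scan. A reader of the imaging sentence would expect a complete-case ANOVA in people who finished the programme.

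The reasoning also runs backwards. The mixed model is preferred elsewhere because it copes with missing data, and it is dropped for the outcome with the most missing data. The stated reason is observed drop-out, so the analysis set appears to have been chosen after the losses were known.

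What is at stake is selection. Finishing the intervention and returning for tests and a scan all happen after randomisation and may be related to arm and to prognosis. Restricting the comparison to people who did so weakens the protection that randomisation gives, for an outcome meant to carry primary evidence.

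**Working it through.** **1. The article's own percentages.** Table 2 gives 28 randomised to MAP and 27 to HEP; Section 4.3 gives the losses.

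- MAP: 18/28 = 64.29%. HEP: 21/27 = 77.78%. Both agree with the text, so the denominators are all randomised participants.

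**2. How many remain.**

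- MAP: 28 − 18 = 10 (10/28 = 35.7%).
- HEP: 27 − 21 = 6 (6/27 = 22.2%).
- Total: 16/55 = 29.1%.

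This is derived, not stated, and it is an upper limit for the per-protocol set: participants must also have completed the intervention and have follow-up neurocognitive tests.

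**3. Is missingness worst for imaging?** Losses in both arms over 55:

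| Measures | Lost | Share |
|---|---|---|
| Fluid biomarkers | 9 + 6 = 15 | 27.3% |
| Psychometric | 10 + 8 = 18 | 32.7% |
| Neuroimaging | 18 + 21 = 39 | 70.9% |

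Yes, by more than a factor of two.

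**4. The statements side by side.**

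| Place | Method for imaging | Who is included |
|---|---|---|
| Abstract | Linear mixed model | Not stated |
| 3.10, imaging sentence | ANOVA | Completers with follow-up tests and scans |
| 3.10, general rule | Not stated | Anyone measured at least once |

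The first two rows conflict on method and the last two on population.

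**5. What the general rule would give.** The number with at least one scan lies between 16 and 55. The text does not say how many had a baseline scan, so it cannot be narrowed.

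**6. Completion is not defined.** Section 3.6 runs weekly sessions to 3 months and boosters to 9 months. If completion means 9 months, inclusion depends on events after the last scheduled scan. If it means 3 months, it does not.

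**7. Precision, for context only.** The effect size of 0.5 in Section 3.10 was set for other outcomes; using it for imaging is an assumption. Two-sided 5%, two-sample t-test:

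- 10 v 6: power 15%; effect detectable with 80% power, 1.56 SD.
- 28 v 27 (everyone scanned at follow-up): power 44%; detectable effect 0.77 SD.
- Standard error ratio: √[(1/10 + 1/6) / (1/28 + 1/27)] = 1.91.

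The gap between these rows comes from scans that do not exist, not from the choice of analysis set.

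**The case against.** **The exception is disclosed.** Section 3.10 ties intention-to-treat to the psychometric and fluid measures, then states and explains the imaging exception. The paragraph with the general rule opens on the mixed models, so the rule could be read as covering only those. This makes the population conflict partly one of wording. It still stands, because the sentence is written without limit, and the Abstract's method statement conflicts with the ANOVA in any case.

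**A reader might infer that the imaging comparison is no longer randomised.** The documents do not support that. Arms are compared as assigned, and Section 4.2 says that all participants attended their assigned group. MRI consent was optional (Section 3.2). Refusals made before randomisation would leave a randomised comparison among those who agreed. How the 39 divide between refusal and later loss is not in the text; Figure 4, which is not shown here, may give it.

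**A reader might infer that retention differs by arm.** 35.7% v 22.2% is compatible with chance (Fisher's exact p = 0.38).

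**A reader might blame the per-protocol choice for low power, or say that baseline scans are thrown away.** The power figures reflect missing scans and a borrowed effect size. Nothing shows that completers' baseline scans go unused; only scans from people outside the set are lost to the analysis.

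**A reader might infer a 9-month imaging claim.** No section makes one specifically. The Abstract's three-visit sentence is a summary that Table 1 qualifies, so a wording correction is enough.

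**The remedy may change little.** With one follow-up scan and baseline entered only as a covariate, as Section 3.10 describes for its models, people with a baseline scan alone add nothing to the treatment contrast. This is correct, and the fix must take account of it.

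**Conclusion.** The concern holds as a contradiction about a declared primary outcome and as an avoidable selection step. Imaging is described as analysed by mixed models (Abstract) and by ANOVA (Section 3.10), and as following intention-to-treat and as restricted to completers (both Section 3.10). The restriction leaves at most 16 of 55 randomised, 10 v 6.

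The conclusion rests on reading the Section 4.3 losses against all randomised participants, which the percentages confirm, and on taking them as 3-month losses, which Table 1 implies. The direction and size of any bias cannot be judged from the documents: the numbers scanned but excluded as non-completers, and the numbers who never agreed to MRI, are not in the text.

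Imaging's primary status is itself unsettled, since the Abstract includes it and the sample-size paragraph of Section 3.10 does not.

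**What to change.** - Make the main imaging analysis a likelihood-based mixed model by assigned arm, in all randomised participants with at least one scan. Do not require completion of the intervention or of the neurocognitive tests.
- Enter baseline and 3-month scans both as outcomes, so that people with only a baseline scan contribute. State the missing-at-random assumption.
- Keep the per-protocol ANOVA as a labelled sensitivity analysis, and define completion for it.
- Correct the general intention-to-treat sentence in Section 3.10 and the method statement in the Abstract.
- State that imaging is a 3-month outcome with no 9-month scan, as in Table 1.
- Reconcile the Abstract's primary outcomes with the co-primary outcomes in Section 3.10. If imaging's label changes at this stage, say that this was done after data collection.

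**Cost.** Some re-analysis of existing scans and a few sentences; no new data. Intervals will stay wide: the model removes the completer selection but does not recover missing scans or much power.

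### As written, the linear mixed model uses the baseline value twice, as an outcome row and as a covariate, so standard errors for the arm difference at a follow-up visit are too small

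*Protocol article*

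**What the plan says.** All of this is in section 3.10 of the protocol article, except the visit schedule.

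- **Span of the outcome.** Treatment effects on biomarkers and psychometric scales are assessed "compared to the active control group, HEP, over the three time-points". Table 1, captioned "A summary of assessments or measures collected throughout the three time-points", has columns for baseline, 3 months and 9 months.
- **Fixed effects.** "The time-points of the intervention, treatment arm, and an interaction term between time-points and treatment arm were treated as the independent variables".
- **Who is included.** "The model considers all the participants included in the baseline, regardless of whether they have missing values at subsequent follow-ups". The next paragraph says that "all the participants who had measures at at least one time-point were included in the analysis".
- **Covariates.** "Covariates for all the models included the baseline values of the respective outcome variable, age, sex, and years of formal education".

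The article names no covariance structure. It also does not say which coefficient (arm, time by arm, or arm at a visit) is the treatment effect.

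**The concern.** A participant with only a baseline value can contribute to a mixed model only if baseline is one of the responses. The inclusion rule and the three time-points therefore make baseline an outcome row, and the covariate list puts the same number on the right-hand side.

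One slope must then serve two kinds of row. For the baseline row the true slope on baseline is 1. For a follow-up row it is the between-visit correlation. The pooled slope fits neither, and the residual variance differs sharply between visits by construction.

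This is the stated analysis for all psychometric and fluid-biomarker outcomes, which include the co-primary outcomes. If the arm difference at 3 or 9 months is read from this model, its confidence interval is too narrow and its p-value too small.

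**Working it through.** The article gives no standard error or error rate for this model, so there is no figure of its own to reproduce.

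**Inputs from the article.** 28 v 27 participants (Table 2). Three visits (Table 1). Two-sided 5% level (section 3.10). Lost by 9 months (section 4.3): psychometric (10 + 8)/55 = 32.7%; fluid biomarkers (9 + 6)/55 = 27.3%.

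**Assumptions not in the article.** Unit variance at each visit, equal between-visit correlation ρ of 0.5 to 0.7, a random-intercept fit, data missing completely at random, and a varying share of the loss already present at 3 months. Age, sex and education are left out.

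**Step 1: arm difference at 9 months, complete data.** Baseline Y0 is constant within a person, so its fitted slope is that of the person's three-visit mean on Y0:

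b = (1 + 2ρ)/3.

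Residual variances about that slope:
- baseline row: (1 − b)²
- follow-up row: 1 − 2bρ + b²

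A random-intercept model gives every visit the average of these, (baseline + 2 × follow-up)/3. The model SE divided by the true SD is √(average ÷ follow-up), and the approximate rejection rate is 2{1 − Φ(1.96 × ratio)}.

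| ρ | b | baseline row | follow-up row | average | SE ratio | rejects |
|---|---|---|---|---|---|---|
| 0.5 | 0.667 | 0.111 | 0.778 | 0.556 | 0.845 | 9.8% |
| 0.6 | 0.733 | 0.071 | 0.658 | 0.462 | 0.838 | 10.0% |
| 0.7 | 0.800 | 0.040 | 0.520 | 0.360 | 0.832 | 10.3% |

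At ρ = 0.6 the true SD is √(0.658 × (1/28 + 1/27)) = 0.219 and the model SE is √(0.462 × (1/28 + 1/27)) = 0.183. REML simulation agrees: SE 15–18% too small, rejection about 9–11%.

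**Step 2: the other two tests, complete data.** The time-by-arm contrast at 9 months is the arm difference in Y9 − Y0, from which the covariate cancels. Its true variance factor is 2(1 − ρ) = 0.80 at ρ = 0.6.

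The model uses 2 × (average variance − average covariance). The residual covariances are (1 − b)(ρ − b) = 0.267 × (−0.133) = −0.036 for baseline with each follow-up, and ρ − 2bρ + b² = 0.258 between follow-ups. Their average is (2 × (−0.036) + 0.258)/3 = 0.062, so the model has 2 × (0.462 − 0.062) = 0.80, the same value.

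The arm main effect reduces to a regression of person means on arm and baseline, which is also sound. Simulation gives 4.2–5.6% for both tests.

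**Step 3: with dropout.** Simulation, no true effect, one third lost by 9 months, at least 1500 runs per setting:
- arm difference at 9 months: about 11–14%
- arm main effect: about 6–11%
- time by arm: about 6–9%
- baseline used once (3 and 9 months as responses), arm difference at 9 months: about 5–6%

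The ranges for the main effect and the interaction depend mainly on how much loss had already occurred at 3 months. One setting in detail (ρ = 0.6, 33% missing at 9 months): true SD 0.272 against mean SE 0.214 for the 9-month arm difference, rejecting 12.4%. With baseline used once the figures are 0.265 and 0.262, rejecting 5.5%.

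**Step 4: a freer covariance does not rescue the model.** If baseline has its own residual variance, that variance goes to zero as b goes to 1, and the likelihood has no maximum. In a test data set the log-likelihood with unstructured covariance, up to a constant, rose from 70 at slope 0.5 to 539 at slope 0.9999.

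**Step 5: size of the arm main effect.** Averaged over three visits it estimates (0 + d3 + d9)/3. With d3 = d9 = 0.5 this is 1.0/3 = 0.33. Without the baseline covariate the simulated value is much the same (0.337). The time-by-arm contrast still estimates 0.50.

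**The case against.** The strongest reply is that double use is inferred. The article never states outright that baseline is a response row, and the text could be a loose description of an ordinary baseline-adjusted model of the follow-ups. That is possible. But such a model cannot retain participants who have only a baseline value, which the section says twice, so the text as it stands needs correcting either way.

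The second reply is that the harm is conditional. This stands in part. With complete data and equal correlations the main effect and interaction tests hold their level. The rates under dropout rest on an unstated covariance structure, unstated correlations and an unreported 3-month loss. With the lower fluid-biomarker loss, all of it after 3 months, the interaction rejects about 6% and the main effect about 7%. That the article does not name a covariance structure is not itself a fault.

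A reader might go further in three ways that the article does not support:
- **That the covariate shrinks the efficacy estimate by a third.** The shrinkage comes from averaging over a baseline row. It affects only the arm main effect, which the article does not name as the treatment effect. With complete data it costs no power (78.2% against 78.1%).
- **That the inclusion rule fails for want of baseline values.** Section 3.5 randomises after baseline assessments. Bio-specimens were optional, but no participant with follow-up and no baseline value is reported.
- **That the published results are wrong.** How those models were actually fitted cannot be seen from this article.

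**Conclusion.** The specification is wrong as written. For the arm difference at a follow-up visit the fault is present even with complete data: about twice the nominal error rate (9–11%), rising to about 11–14% with one third lost by 9 months. These figures assume a random intercept and equal correlations of 0.5 to 0.7.

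If correlation decays with time, the rate at 9 months was 14–18%, but part of that comes from the misfitting covariance and not from the double use.

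It would be too strong to say that every p-value from this model is wrong. For the arm main effect and the time-by-arm term, inflation appears with dropout and varies with its timing. The two-thirds figure is a separate consequence of keeping baseline as an outcome row, and it concerns the main effect only.

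**What to change.** Use baseline once, in one of two ways:

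- **(a)** Model only the 3- and 9-month values as responses, with baseline as covariate and time, arm and time by arm as terms.
- **(b)** Model all three visits as responses, with arm means constrained equal at baseline and no baseline covariate.

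Name the arm difference at a stated visit, for example 9 months, as the treatment effect. Under (a) the time-by-arm term must not be the efficacy test: it only compares 9 with 3 months and has about 5% power against a constant effect.

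Correct the wording of section 3.10, including the inclusion statements if (a) is chosen. Use the corrected model for the pending analyses, and re-run any completed analysis that was fitted as described.

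The cost is a few lines of SPSS syntax and no new data. Under (a), participants without any follow-up value leave the likelihood, but they carry essentially no information on the arm effect.
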